European guidelines recently incorporated FeNO as an effective alternative and cost-effective diagnostic tool for asthma and to optimise access to specialised testing : a FeNO level ≥40 ppb is 90% specific for asthma diagnosis in adults.^29 30^ The United Kingdom’s National Institute for Health and Care Excellence (NICE) guidelines recommend using FeNO and BEC early in the diagnostic algorithm as a first-line diagnostic tool before spirometry or peak flow monitoring.^29 30^ In children ≥5 years, only FeNO (≥35 ppb) has been validated as a first-line diagnostic test, while BEC had been used after BDR and PEF, along with skin prick tests or specific IgE measurement.^29 31^ The introduction of FeNO testing as a first-line diagnostic tool is estimated to enable approximately 29 000 additional asthma diagnoses annually, leading to earlier treatment initiation, improved disease control, reduced absenteeism and potential cost savings of £100–204 million per year.^32^

In Quebec, over 3000 diagnostic tests are still pending across Centre Hospitalier Universitaire de Sherbrooke (CHUS), CHU Sainte-Justine (CHUSJ) and the Montreal Children’s Hospital (MHC), including 1300 tests for children, with wait times exceeding 1 year. BPTs are scheduled chronologically, with priority only for internal referrals, that is, for specialists of the institution. The lack of robust prospective data on FeNO and eosinophils (and limited FeNO access) has restricted their integration into diagnostic algorithms.

Our overarching aim is to address an evidence gap by evaluating the integration of inflammatory biomarkers into referral for the asthma diagnosis specifically from primary or community care under real-world conditions. Specifically, we aim to assess whether FeNO and BEC can improve the prioritisation of patients for bronchial provocation testing (BPT), thereby streamlining referrals and supporting more timely and cost-effective asthma diagnosis. Propulsion Santé also includes two translational sub-studies: DIVE (in adults) and DIVE-2 (in children) involving additional sampling (serum and nasal epithelial lining fluid (NELF)) to link inflammatory mediators (alarmins, interleukins and eicosanoids), diagnosis and T2 biomarkers to gain mechanistic insight at the point of diagnosis in primary care.

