### Setting

The study will be conducted at three Quebec medical centres: CHUS, CHUSJ and MHC-MUHC. A dedicated research respiratory therapist will be assigned to each centre for 1 year to facilitate recruitment through convenience sampling. With participant consent, longitudinal follow-up by email will occur at 4, 8 and 12 months after the initial diagnostic visits.

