### Participants

Eligible participants are individuals aged ≥6 years who present with symptoms suggestive of asthma and have been referred by primary care (family physicians and nurse practitioners) or community practice (eg, paediatricians and other non-pulmonologist physicians) for asthma diagnosis at one of the three participating centres. Participants are identified from an existing waiting list of approximately 3000 patients awaiting respiratory function testing. The only exclusion criterion for PROPULSION SANTÉ is refusal to participate in the study.

Among these patients, a target sample of 123 adult participants (aged≥18 years) and 123 paediatric participants (aged 6–18 years) undergoing BPT will be consecutively invited to participate in the DIVE and DIVE-2 sub-studies, respectively, regardless of their T2 status. DIVE/DIVE2 inclusion requires non-diagnostic spirometry and no contraindication to methacholine challenge. Patients will be excluded from participation if they meet any of the following conditions: use of inhaled or systemic corticosteroids within 48 hours prior to testing; tobacco use within the previous 6 hours; diagnosis of chronic obstructive pulmonary disease (COPD), defined as all of the following — age ≥40 years, fixed airway obstruction on spirometry (FEV1/Forced Vital Capacity (FVC)<0.7) and a smoking history >10 pack-years or documented alpha-1 antitrypsin deficiency— and evidence of parenchymal lung disease (such as cystic fibrosis or bronchiectasis), unstable cardiac disease or a history of acute respiratory infection (viral or bacterial) within the preceding 4 weeks.

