### Study visits

Study visits will coincide with medically recommended testing for suspected asthma (pre-/post-bronchodilator spirometry followed, if negative, with methacholine). Biobanking for DIVE and DIVE2 will only be conducted during methacholine visits. Electronic informed consent (and assent when applicable) will be obtained via REDCap.^33 34^ Additional data will be gathered on asthma exacerbation history and healthcare resource utilisation over the preceding year, including medications, by the use of reMed,^35^ a provincial research data repository of community pharmacy dispensed drugs that covers individuals under the public drug insurance plan.

During the single study visit, baseline bio-anthropometric and clinical data (age, sex, ethnicity, height and weight) will be collected. Participants will be interviewed regarding their medical history (smoking status, respiratory medication (with simultaneous carbon footprint calculation based on the number and type of inhalers delivered), recent (< 6 last weeks) respiratory infection and allergic history. Patients (and their legal guardian, if applicable) will complete standardised questionnaires on asthma control for the last 4 weeks (Asthma Control Questionnaire 5 (ACQ-5),^36^ Asthma Control Test (ACT)^37^ in adults and childhood Asthma Control Test (c-ACT) for children^38^ and of quality-adjusted life years (QALY) (EuroQol Five Dimensions Five Levels (EQ-5D-5L)^39 40^ for adults and EuroQol Five Dimensions Youth (EQ-5D-Y)^41^ for children).

Research respiratory therapists will first measure FeNO during a 10 s exhalation (6 s for children unable to cooperate, with a 10- s expiration)^31 42^ using NIOX VERO device (approved by Health Canada as a clinical tool). The latter was selected based on its established precision (coefficient of variation <10%), reproducibility and clinical validation.^43 44^ Then, blood samples will be collected for BEC either via capillary puncture (preferred for children), using the single-use Tasso+blood collection device (approved by Health Canada), or by venipuncture.^45^ For children, an anaesthetic cream, Ametop GEL 4% (tetracaine hydrochloride gel), will be offered to be applied to the puncture site 30 min before blood collection.^46^

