### Intervention

The interpretation of respiratory function tests and biomarkers will be performed by the principal investigator pulmonologist at each centre or by trained designated collaborating pulmonologists by following these models:

High-risk inflammatory asthma is defined by FeNO ≥25 ppb or BEC ≥300 cells/µL in participants ≥12 years (≥20 ppb or ≥300 cells/µL in children aged 6 to <12 years)^15 50^ : one or more elevated biomarkers will be interpreted as a high risk of asthma exacerbation. If spirometry is non-diagnostic, BPT will be prioritised (<2–4 weeks).Low risk inflammatory asthma is defined by FeNO <25 ppb and BEC <300 cells/µL (<20 ppb or <300 cells/µL in children aged 6–<12 years)^15 50^: this will be interpreted as a low risk of asthma exacerbation. If spirometry is non-diagnostic, BPT will be scheduled according to the standard waiting list.

Results of biomarkers will be integrated on the medical report indicating the probability (high/low) of asthma exacerbation and suggested management with either ICS taken as-needed (T2-low) or regularly (T2-High) ICS if clinically appropriate, which will be forwarded to the referring physician.

The patient test pathway based on their respiratory test and the results of the inflammometry assessment is summarised in figure 2.

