**Figure 2 F2:**
[figure not shown]
Flow Diagram. Patients with suspected asthma are referred by primary care for pulmonary function testing (BDR or BPT). Those who consent to participate in the study will undergo BEC and FeNO testing. Patients with normal spirometry results and at least one elevated inflammatory marker will have their methacholine challenge test prioritised. If no inflammatory markers are elevated, the BPT will be scheduled within standard timelines. Patients undergoing a BPT—either directly on referral or after an initial BDR—will be invited to participate in the translational research studies, DIVE for adults or DIVE2 for children. Patients with a confirmed diagnosis of asthma (based on spirometry or BPT) will also be stratified according to their inflammometry results, which will be included in the report sent to the referring physician. BEC, blood eosinophil count; BDR, bronchodilator reversibility; BPT, bronchial provocation testing; FeNO, fraction exhaled of nitric oxide.

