Our study evaluates the effectiveness of current asthma diagnostic methods in Canada and proposes improvements in Canada. The anticipated outcomes are multifaceted: (1) improved equity in healthcare access through better prioritisation; (2) enhanced patients outcomes by enabling early identification and treatment of individuals with elevated inflammation, thereby reducing exacerbations and lung function decline; (3) organisational and economic efficiency through reduction of costly tests and unnecessary consultations; (4) generation of novel paediatric data; (5) integration of environmental considerations through reduction of inhaler-related emissions.^28 79^

An additional strength of the present project is the integration of two complementary translational substudies—DIVE (in adults) and DIVE 2 (in children)—which provide a unique opportunity to link clinical inflammatory phenotypes with underlying molecular profiles through the collection of NELF and serum samples, and the quantification of key inflammatory proteins (eg, alarmins, interleukins and chemokines). Patients are not pre-selected by T2 phenotype, as these studies are designed as real-world primary care studies. Maintaining the distribution of T2-high and T2-low patients, as observed in the general population, allows assessment of biomarker performance under real-world conditions. These sub-studies will help identify potential biomarkers associated with type 2 inflammation and final asthma diagnosis. By incorporating both paediatric and adult populations, this integrated approach enhances the relevance and applicability of findings and supports the development of precision diagnostic tools that are biologically grounded and clinically actionable.

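### Sampling only at the methacholine visit, which T2-high patients reach sooner after a non-diagnostic BDR, tends to over-represent them in DIVE/DIVE2, so the design does not secure the claimed T2 mix

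*Protocol article*

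**What the plan says.** The Discussion states that sub-study patients are not selected on T2 phenotype and gives the reason: "Maintaining the distribution of T2-high and T2-low patients, as observed in the general population, allows assessment of biomarker performance under real-world conditions". The Participants section supports this with consecutive invitation at BPT that ignores T2 class.

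Three other sections determine who is there to be invited.

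- **Study visits:** "Biobanking for DIVE and DIVE2 will only be conducted during methacholine visits".
- **Intervention, at least one raised biomarker:** "If spirometry is non-diagnostic, BPT will be prioritised (<2–4 weeks".
- **Intervention, no raised biomarker:** "If spirometry is non-diagnostic, BPT will be scheduled according to the standard waiting list".

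The Introduction describes the pending tests as "including 1300 tests for children, with wait times exceeding 1 year". The Setting section says: "A dedicated research respiratory therapist will be assigned to each centre for 1 year to facilitate recruitment through convenience sampling".

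On eligibility, the Participants section says "DIVE/DIVE2 inclusion requires non-diagnostic spirometry and no contraindication to methacholine challenge". The Figure 2 legend extends the invitation to patients who come to BPT "either directly on referral or after an initial BDR".

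**The concern.** The invitation rule is neutral on T2 class, but the queue leading to it is not. Among patients who arrive after a non-diagnostic BDR, the biomarker result decides how soon they reach the only visit at which samples are taken. Over any limited recruitment period, more of the T2-high than of the T2-low patients will have got there. If triage works as the parent study intends, this follows directly.

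The sub-studies measure mediators of the T2 pathway (among them IL-4, IL-5, IL-13, TSLP, TARC and eotaxin-3) and relate them to the asthma diagnosis. T2 class is correlated with those mediators. Over-sampling T2-high patients among both asthmatics and non-asthmatics raises apparent sensitivity and lowers apparent specificity. The Discussion gives real-world performance as the reason for not selecting on T2, so the stated purpose is affected. The Statistical methods, the Sample size section and the limitations in the Discussion describe no quota or weighting that would offset this.

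**Working it through.** **The plan's own figure.** The document gives no expected T2 mix. Its one quantitative statement for the sub-studies is N = 123, 90% power, AUC 0.7 against 0.5, two-sided alpha 0.016, ratio 2:1 (82 positive, 41 negative). With the Hanley-McNeil variance, Var = [A(1−A) + (n1−1)(Q1−A²) + (n0−1)(Q2−A²)]/(n1·n0), Q1 = A/(2−A), Q2 = 2A²/(1+A), the standard errors are 0.055 at A = 0.5 and 0.048 at A = 0.7. Power is Φ[(0.2 − 2.41 × 0.0554)/0.0475] = 91.9%. The sample size reproduces and is not in question.

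**Inputs for the T2 mix**

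- T2-high wait after a non-diagnostic BDR: taken as 1 month (Intervention gives under 2–4 weeks).
- T2-low wait W: not given for this step, so varied from 3 to 12 months. The Introduction reports waits above 1 year for pending tests.
- Window: 12 months, borrowed from the parent study (Setting, Sample size). DIVE's own window is not given.
- Natural T2-high share p: 50%, an assumption. The Introduction gives about half for asthmatics, not for suspected cases.
- Direct-to-BPT share d: not given; 0 and 0.5 are shown.
- Backlog: W months of patients listed before triage, in natural mix, served in addition to new patients. This is an assumption, prompted by the existing list of about 3000 (Participants) and the added therapists (Discussion).

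**Formula.** With uniform inflow of one patient per month:

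- H = p[12d + (1−d)(11 + W)]
- L = (1−p)[12d + (1−d)(12 − W + W)] = 12(1−p)
- T2-high share = H/(H + L)

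| W (months) | d = 0 | d = 0.5 |
|---|---|---|
| 3 | 7.0/13.0 = 54% | 6.5/12.5 = 52% |
| 6 | 8.5/14.5 = 59% | 7.25/13.25 = 55% |
| 9 | 10.0/16.0 = 63% | 8.0/14.0 = 57% |
| 12 | 11.5/17.5 = 66% | 8.75/14.75 = 59% |

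**Dependence on the backlog.**

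- Fixed capacity, W = 12, d = 0: new T2-high patients take 5.5 of 12 slots and backlog fills 6.5, half of them T2-high. The share is (5.5 + 3.25)/12 = 73%. With d = 0.5 it is (3 + 4.375)/12 = 61–62%.
- No backlog at all, so L = (1−p)[12d + (1−d)(12−W)] and H has 11 in place of 11 + W: 55%, 65%, 79% and 100% for W = 3, 6, 9 and 12 with d = 0; 52%, 56%, 61% and 66% with d = 0.5; 51%, 53%, 55% and 57% with d = 0.75.

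The share stays at its natural value only if every patient comes directly to BPT or T2-low patients wait no longer than T2-high patients.

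**Effect on accuracy measures.** In the backlog model the sampling rate of T2-high relative to T2-low patients is k = d + (1−d)(11 + W)/12. At W = 12 this is 1.92 (d = 0) or 1.46 (d = 0.5). As an illustration, take a binary marker that coincides with T2 class, with assumed true sensitivity s = 0.50 and specificity c = 0.80. Observed sensitivity is ks/(ks + 1 − s), observed specificity is c/[c + k(1 − c)], and the AUC of a binary marker is their mean.

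| k | Sensitivity | Specificity | AUC |
|---|---|---|---|
| 1 | 0.50 | 0.80 | 0.650 |
| 1.5 | 0.60 | 0.73 | 0.664 |
| 2 | 0.67 | 0.67 | 0.667 |

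The AUC moves by at most 0.017 here, about a third of the standard error of 0.048.

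**The case against.** The strongest reply is that the invitation rule is what the Discussion describes. Nobody is chosen or refused on T2 class, and that is true. It does not rescue the sentence about the distribution, because selection happens before invitation.

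Four further objections limit the point, and they stand.

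- A year-long wait implies a standing list being served during the window. Patients listed before triage arrive in natural mix. A reader who starts from an empty queue might infer that the sub-studies could become entirely T2-high. That figure requires no backlog, no direct referrals and a 12-month T2-low wait together, and the document describes a large existing list.
- The 12-month limit belongs to PROPULSION SANTÉ. DIVE and DIVE2 were designed earlier and have their own registrations. Samples taken before triage began, or after T2-low patients catch up, dilute the effect.
- A reader might take the Participants section and the Figure 2 legend as a flat contradiction. Both can hold if patients referred directly to BPT already have non-diagnostic spirometry. What is unclear is the status of direct referrals without it.
- The sub-study sample size is built on AUC, and enrichment in both cases and controls largely cancels there in the worked example. The material does not support a claim that the planned AUC tests are invalid.

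These points reduce or blur the size. They do not remove the direction wherever some patients arrive after BDR and T2-low patients wait longer.

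**Conclusion.** The design does not secure the statement that the T2-high/T2-low mix is maintained, and the likely error is towards too many T2-high patients. Under a natural share of 50%, a 12-month window and an untriaged backlog, the sampled share is about 54–66% with no direct referrals and 52–59% with half direct. It is higher if little backlog is served and close to natural if most referrals are direct. The direct share, the T2-low wait, the backlog served and the DIVE window are all unstated, so these are ranges under assumptions and not predictions.

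Sensitivity and specificity of T2-pathway mediators are the measures at risk. The AUC may change little. The finding concerns the sub-studies and what is claimed for them; it does not touch the parent study's primary outcome.

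**What to change.** 1. Weight the DIVE and DIVE2 ROC and regression analyses by the inverse probability of reaching a sampled BPT, by T2 class and referral route (direct or after BDR). The reference group should be PROPULSION SANTÉ participants with non-diagnostic spirometry who are eligible for BPT.
2. Report the sub-study T2 mix beside that of the reference group.
3. If too few T2-low post-BDR patients are sampled for weighting to work, report results by T2 stratum.
4. If a quota is preferred to weighting, set it from the same reference group. The mix of all first-visit patients is the wrong target because it includes patients already diagnosed by BDR, who cannot enter the sub-studies.
5. State in the Participants section and the Figure 2 legend whether patients sent directly to BPT without prior spirometry are eligible.
6. Qualify or remove the Discussion sentence on the maintained distribution.

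The cost is low. FeNO and BEC are already measured throughout the parent cohort, no extra patients are needed, and clinical scheduling is untouched. Confidence intervals will be somewhat wider; with a quota, the T2-low places would fill more slowly.

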## Conclusion

This innovative multicentre observational study is the first to assess the real-world application of inflammatory biomarkers in the asthma diagnostic test pathway among both paediatric and adult populations referred from primary care. By prospectively evaluating FeNO and BEC and comparing with conventional lung function tests, we aim to inform a more efficient and evidence-based system for prioritising suspected asthma cases.

Biomarker-guided stratification appears promising to reduce diagnostic delays in patients with inflammatory phenotypes, thus minimising unnecessary treatment in non-asthmatic individuals and improving clinical outcomes through recommendations for targeted interventions. The study will provide solid evidence to refine age-specific biomarker cut-offs for diagnostic purposes, addressing the current scarcity of validated thresholds in the paediatric population and improving understanding of biomarker performance across diverse demographic groups.

By enhancing diagnostic accuracy and resource efficiency while supporting personalised care, this project will advance the principles of precision medicine. It integrates accessible biomarker tools into routine clinical practice, offering a scalable strategy to streamline diagnosis, control healthcare costs, potentially reduce the environmental impact of unnecessary inhalers used during diagnostic delays and foster a more sustainable and cost-effective approach to respiratory care.

## Data Availability

Data are available upon reasonable request.
